### Study Procedure

The specific measurements and time points for data collection of this study are outlined in Figure 2. Eligible subjects will undergo a 1-week preintervention screening period and a 24 weeks treatment period. After the research commences, all subjects enrolled will be followed up every 4 weeks for 24 weeks. All subjects will be informed about the oral and written information about this trial and asked to sign informed consent forms.

**FIGURE 2 F2:**
[figure not shown]
Clinical Study Visit Form. 1 Only for childbearing-age women and secondary amenorrhea women for more than 1 week; Test should be initiated within 24 h prior to the first medication. 2 Blood sample of the glycosylated hemoglobin will be collected and placed in –80°C refrigerator. 3 Only 120 subjects in four centers (Peking Union Medical College Hospital, Beijing Hospital, Affiliated Hospital of Qingdao University, Huashan Hospital Affiliated to Fudan University) will receive this test.

## Outcome Measure

### Demographic Information

Demographic information such as gender, age, course of disease, previous medical history will be collected.

## Efficacy Outcomes

### Primary Outcomes

Changes in total score on the MDNS Scale: The changes of MDNS will be compared in the two groups prior to and following Mudan granule administration. The total score is 46, ranging from 0 (least severe) to 46 (most severe). Measurement will be performed at baseline and week 12, 24.

### Secondary Outcomes

1. Changes in NCV: The changes in NCV of each nerve will be compared in the two groups prior to and following Mudan granule administration. Measurement will be performed at baseline and week 24.2. Changes in corneal nerve fiber density of each mm^2^: The changes in corneal nerve fiber density of each mm^2^ will be compared in the two groups prior to and following Mudan granule administration. Measurement will be performed at baseline and week 24.3. Changes in corneal nerve branch density of each mm^2^: The changes in corneal nerve branch density of each mm^2^ will be compared in the two groups prior to and following Mudan granule administration. Measurement will be performed at baseline and week 24.4. Changes in corneal nerve fiber length of each mm^2^: The changes in corneal nerve fiber length of each mm^2^ will be compared in the two groups prior to and following Mudan granule administration. Measurement will be performed at baseline and week 24.5. Changes in total score on the Toronto Clinical Scoring System(TCSS) Scale: The changes of toronto clinical score will be compared in the two groups prior to and following Mudan granule administration. The total score is 19, ranging from 0 (least severe) to 19 (most severe). Measurement will be performed at baseline and week 12, 24.6. Changes in total score on the TCM Syndromes Efficacy Score Scale: The changes in TCM syndromes efficacy score will be compared in the two groups prior to and following Mudan granule administration. TCM syndromes efficacy score is 45, ranging from 0 (least severe) to 45 (most severe). Measurement will be performed at baseline and week 4,8,12,16,20,24.7. Changes in total score on the Clinical Symptoms Score Scale: The changes of each clinical symptom score will be compared in the two groups prior to and following Mudan granule administration. Clinical symptom score ranging from 0 (least severe) to 6 (most severe). Clinical symptoms mainly included pain, numbness, and paresthesia. Measurement will be performed at baseline and week 12, 24.

### Monitoring Outcomes

1. Fasting blood glucose, and blood pressure. Measurement will be performed at baseline and week 4,8,12,16,20,24.2. Glycated hemoglobin, and blood lipid. Measurement will be performed at baseline and week 12, 24.

### Safety outcomes and adverse events.

1. Adverse events: adverse events will be monitored for 6 months from the time the subjects enrolled in the study to the last follow-up. All information about adverse events will be carefully recorded at any time, such as their intensity, duration and relationship with the Mudan granule. The intensity of adverse events will be categorized as light, moderate and heavy. Serious adverse events must be reported immediately to the research center, the main research medical ethics committee, and the primary sponsor. At the same time, it will be reported to the National Medicinal Product Administration (NMPA) within 24 h. In addition, a Serious Adverse Event Form must be completed as soon as possible.2. General vital signs: body temperature, heart rate, respiration and so on. Measurement will be performed at baseline and week 4,8,12,16,20,24.3. Blood routine, urine routine, urine pregnancy test, stool routine, 12-lead Electrocardiography, hepatic and renal function tests. Measurement will be performed at baseline and week 12, 24.

### Sample Size Calculation

Depending on the previous study (Li and Yu, 2016) of Mudan granule combined with methylcobalamin in the treatment of DPN with 12 weeks intervention, the results of the MDNS indicated that the study group (Mudan granule + Methylcobalamin) scale score was 5.48 ± 1.19, the control group (Placebo + Methylcobalamin) scale score was 8.21 ± 1.24, and the mean difference between the two groups was 2.73; Assuming that Mudan granule combined with methylcobalamin in the treatment of DPN can reduce the MDNS by 0.58 after 12 weeks of intervention, it is considered more effective than the control group. Taking *α* = 0.05, *β* = 0.10, the intervention group and the control group with 24 weeks intervention were allocated at a ratio of 1:1. The sample size calculated by the Power Analysis and Sample Size (PASS) 11 software is not less than 167 cases in each group. Considering that an expected withdrawal rate does not exceed 20%, the target sample size is set at 402, with 201 cases in each group.

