### Statistical Analysis Method

SAS 9.4 will be employed for statistical calculations. All data statistics will be analyzed by using a bilateral test, and *p* ≤ 0.05 suggested statistical significance. Count data will be expressed by the constituent ratio. The description of the quantitative data will use the mean, standard deviation, median, and minimum/maximum values. All indicators will be analyzed using appropriate statistical methods. Comparisons between groups of quantitative data will be performed using the Wilcoxon rank-sum test and group *t*-test. The main efficacy indicators will be described with the diachronic statistical description. Analyses of covariance with baseline as a covariate will be used to adjust for comparisons between groups. If necessary, the center effect may be considered and the least square means (LS-means) with their 95% confidence intervals (95% CI) for each group will be calculated. Chi-squared or Fisher’s exact test will be used for categorical data, while grade data will be analyzed by the CMHχ^2^ test or Wilcoxon rank-sum test.

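### The 167 per group at 90% power cannot be reproduced from the inputs printed with it, which give 94 per group; at those inputs 167 per group has about 99% power

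*Protocol article*

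**What the plan says.** The Sample Size Calculation section of the protocol article starts from an earlier 12-week study of the same combination. For the study group it reports that the MDNS "scale score was 5.48 ± 1.19", and it continues: "the control group (Placebo + Methylcobalamin) scale score was 8.21 ± 1.24, and the mean difference between the two groups was 2.73". It does not plan on the observed 2.73. It sets a smaller target, that the combination "can reduce the MDNS by 0.58 after 12 weeks of intervention, it is considered more effective than the control group".

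The error rates follow: "Taking *α* = 0.05, *β* = 0.10", with 1:1 allocation. The result is given as: "The sample size calculated by the Power Analysis and Sample Size (PASS) 11 software is not less than 167 cases in each group". That figure is then raised to 201 per group, 402 in all, for withdrawal of up to 20%.

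The section does not state sidedness, but the Statistical Analysis Method section does: "All data statistics will be analyzed by using a bilateral test". The article gives no MDNS standard deviation other than 1.19 and 1.24. It names no test procedure for the calculation and no correlation between baseline and follow-up.

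**The concern.** The section reads as a complete calculation: spread, difference, error rates, allocation, software and answer. A reader with those inputs should be able to recover the answer, and cannot. The printed number is 167/94 = 1.78 times what the inputs require.

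The trial's size and its 90% power both rest on this paragraph. If the inputs are as printed, the power is understated or the required number is overstated. If 167 is the genuine PASS output at 90% power, it came from something the article does not show. An ethics committee or a reader of the results cannot tell which assumption the 402 patients rest on.

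**Working it through.** **Inputs**
- SDs 1.19 and 1.24, difference 0.58, alpha 0.05, power 1 − 0.10 = 0.90, ratio 1:1: Sample Size Calculation section.
- Two-sided test: Statistical Analysis Method section.

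**Step 1, pooled SD.** √[(1.19² + 1.24²)/2] = √1.4769 = 1.215.

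**Step 2, attempt to reproduce 167.** Normal approximation, per group:

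n = 2 × (z₀.₉₇₅ + z₀.₉₀)² × SD² / difference² = 2 × (1.960 + 1.2816)² × 1.4769 / 0.58² = 2 × 10.507 × 1.4769 / 0.3364 = 92.3, so 93.

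The exact two-sample t calculation (noncentral t) gives 94. The figure of 167 is not reproduced.

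**Step 3, other readings of the printed figures** (exact t, 90% power, two-sided 0.05 unless noted)

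| Reading | n per group |
|---|---|
| SD 1.19 in both groups | 90 |
| SD 1.24 in both groups | 98 |
| One-sided 0.05, SD 1.215 | 76 |
| Prior-study difference 2.73 | 6 |
| 0.58 as a superiority margin, true difference 2.73 (2.73 − 0.58 = 2.15) | 8 |
| Wilcoxon test: 94 × π/3, or 94/0.864 | 98 to 109 (98.4 and 108.8 before rounding) |
| SD of a difference, √(1.19² + 1.24²) = 1.72 | 186 (152 one-sided) |

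None gives 167.

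**Step 4, power of 167 per group on the printed inputs.** The noncentrality is 0.58 / (1.215 × √(2/167)) = 4.36, which gives a power of 0.992. At 201 per group the power is 0.998.

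**Step 5, what 167 at 90% power would need.**
- Keeping the difference at 0.58: SD = 0.58 × √(167/2) / 3.2415 = 1.635 by the normal approximation, 1.630 by exact t.
- Keeping the SD at 1.215: difference = 1.215 × 3.2415 × √(2/167) = 0.431 by the normal approximation, 0.432 by exact t.

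Neither value appears in the article. Changing the power also comes close: at 99% power the printed SDs give 163 (SD 1.215) or 169 (SD 1.24).

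**The case against.** The strongest reply is that 1.19 and 1.24 are reported as results of the earlier study and are never called the SD entered in PASS. The planners plainly did not carry that study over unchanged, since they replaced 2.73 by 0.58, and they may have used a larger SD as well. The article condenses a fuller protocol that may state it. One route exists: the primary outcome is described as a change ("The changes of MDNS will be compared in the two groups prior to and following Mudan granule administration"), and an SD of change built from 1.215 with a baseline-to-follow-up correlation of 0.1 is 1.215 × √(2 × 0.9) = 1.630, which matches step 5. This stands as a possible explanation, so the SD may be unprinted rather than wrong. It does not rescue the paragraph, because neither the correlation nor the resulting SD is stated.

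Three stronger readings are tempting, and the documents do not support them.

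- **That the trial is underpowered.** A reader might infer this by supposing a much larger true SD. The only SDs in the article are 1.19 and 1.24, and with them the discrepancy runs in the safe direction. Even if 20% of 201 withdraw, leaving about 161 per group, the power is about 99%.
- **That the SD or the power is the misstated item.** A difference of about 0.43 would explain 167 equally well, so the text does not identify the faulty item.
- **That SDs of a final score are wrong for a change endpoint.** The Statistical Analysis Method section plans analysis of covariance with baseline as covariate. Under that model, change and final score give the same treatment contrast, and the residual SD does not exceed the within-group SD of the final score.

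**Conclusion.** The point holds as a failure of the printed calculation to reproduce. The stated inputs give 94 per group, against 167 printed. At 167 per group they give about 99% power, against 90% printed. At least one printed input, the sample size or the power is wrong, or the SD used for planning is not the one shown. The article does not say which.

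This rests on a two-sample comparison of means, two-sided alpha 0.05 taken from the analysis section, and the two quoted SDs being the planning SDs. The first two can be varied without recovering 167. The third is the assumption that could fail, and if it does, the defect is an SD that is used but not disclosed. On the inputs as stated, the trial is larger than it needs to be for a 0.58-point difference, so this is an error in a stated size or power figure and not a shortage of power.

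**What to change.** Return to the PASS run and restate the paragraph so that its figures agree. Give the SD actually entered and its source, the difference, the sidedness, the test procedure and the power, with the number per group that follows from them. The SD must come from the record of the calculation or from a cited source. It should not be solved backwards from 167.

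If 1.19 and 1.24 were the planning SDs, there are two consistent statements: a required number of about 94 per group at 90% power, or about 99% power at 167 per group.

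The cost is one re-run and a revised paragraph. Enrolment of 402, the primary outcome and the analysis need not change.

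### The 20% withdrawal allowance does not add up: 201 per group leaves about 160 completers, not the required 167, although the effect on power is small

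*Protocol article*

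**What the plan says.** The Sample Size Calculation section of the protocol article gives three figures in sequence.

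- The required number, from sample size software with α and β set at "0.05, *β* = 0.10" (90% power) and 1:1 allocation, "is not less than 167 cases in each group".
- A withdrawal rate expected to be no higher than 20%.
- The number to be randomised, set in view of that rate: "Considering that an expected withdrawal rate does not exceed 20%, the target sample size is set at 402, with 201 cases in each group".

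The formula that leads from 167 to 201 is not given. Whether the test is one- or two-sided is not stated there either, but the Statistical Analysis Method section says "All data statistics will be analyzed by using a bilateral test".

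**The concern.** An allowance for withdrawal is meant to ensure that the required number is still there after the expected losses. The section calls 167 a minimum and names 20% as the loss it provides for. Removing 20% from 201 leaves fewer than 167, so the three figures cannot all hold.

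What is at stake is how the trial is monitored. Anyone reading the section will take 20% as the withdrawal the trial was sized to absorb. If withdrawal ran at 18% to 20%, the plan would appear intact while the number of completers was already below its own minimum.

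**Working it through.** **Inputs.** All come from the Sample Size Calculation section unless noted.

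- Required per group: 167
- Withdrawal: up to 20%
- Randomised per group: 201 (402 in total)
- Power 90%, α 0.05; two-sided according to the Statistical Analysis Method section
- Difference in Michigan Diabetic Neuropathy Score (MDNS): 0.58
- Standard deviations (SD) from the earlier study: 1.19 and 1.24

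**Step 1: reproduce the plan's 201.** Multiplying by one plus the withdrawal rate gives 167 × (1 + 0.20) = 200.4, rounded up to 201. This is an exact match. The formula is therefore inferred, but step 3 does not depend on it.

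**Step 2: the number that keeps 167.** If a fraction d withdraws, n × (1 − d) remain, so n = 167 / (1 − d) = 167 / 0.80 = 208.75. That is 209 per group and 418 in total, or 8 more per group and 16 more in all than planned. Check: 209 × 0.80 = 167.2.

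**Step 3: what 201 leaves at 20%.** 201 × 0.80 = 160.8, so 160 to 161 per group, which is 6 to 7 below 167. In total, 402 × 0.80 = 321.6 against 2 × 167 = 334.

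**Step 4: the withdrawal that 201 can absorb.** 201 − 167 = 34, and 34/201 = 16.9%.

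**Step 5: the effect on power, conditional on 167 giving 90%.** With a two-sided α of 0.05, the standardised signal at n = 167 must be 1.960 + 1.282 = 3.242, and it scales with √n. No SD is needed.

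- n = 160: 3.242 × √(160/167) = 3.173; 3.173 − 1.960 = 1.213; power 88.7%
- n = 161: 3.242 × √(161/167) = 3.183; 3.183 − 1.960 = 1.223; power 88.9%

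**Step 6: does 167 follow from the printed inputs?** Take n per group = 2 × (SD / 0.58)² × 3.242², rounded up.

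| SD | n per group |
|---|---|
| 1.19 | 89 |
| 1.215 (the two SDs pooled) | 93 |
| 1.24 | 97 |

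To reach 167, the SD would have to be 0.58 × √(167/2) / 3.242 = 1.635, a value that the article does not give. With the pooled SD of 1.215, power at 160 per group would be about 99%. So the 89% in step 5 is not a result on the article's printed inputs. It says only what happens if 167 is accepted as the number that gives 90%.

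**The case against.** **Completers are not the primary analysis population.** The section defining the analysis data sets makes the FAS the main efficacy set. It holds every randomised subject with at least one efficacy result after baseline, and missing primary values are filled by LOCF. Withdrawal, as the protocol defines it, can happen at any time in the 24 weeks, so 20% withdrawal is not a 20% loss from the FAS. This stands, and it limits the point. It does not remove it, for two reasons. MDNS is measured only at baseline and at weeks 12 and 24, so a subject lost before week 12 has no post-baseline MDNS to carry forward. The per-protocol set, used for the secondary efficacy analysis, requires completed treatment and takes the full loss.

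**The 20% is a ceiling.** This is true: at 16.9% or below, even completers reach 167. But the sample size was set with that ceiling in view, so it should hold at the ceiling.

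**The base figure of 167 is itself unexplained, so one point of power is false precision.** Step 6 bears this out as far as power is concerned. The mismatch between 167, 20% and 201 remains whatever lies behind 167.

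**Stronger readings that the article does not support.** A reader might infer that the primary analysis will miss 90% power. That does not follow, because the FAS keeps some withdrawn subjects and the shortfall arises only when withdrawal is between 16.9% and 20%. A reader might also infer that power is 89% on the plan's own assumptions. That does not follow either, because the SD needed for it is not stated and the printed SDs give about 99% at 160 per group.

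**Conclusion.** The allowance is wrong as written. At the 20% withdrawal it names, 201 per group leaves 160 to 161 completers, 6 to 7 below the stated minimum, and the rate that 201 can absorb is 16.9%. This rests only on the three printed figures and on reading 167 as the number to be left after withdrawal, which is the purpose of such an allowance.

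The consequence is small. If 167 gives 90% power, the loss among completers at the 20% ceiling is a little over one percentage point. For the FAS it depends on how many withdrawn subjects have post-baseline data, which the article does not predict. The error gives no reason to doubt the trial's validity or to recruit more patients, but the stated tolerance should be corrected because it may be used to judge attrition.

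**What to change.** Keep 402 and restate the allowance in the Sample Size Calculation section in one of two ways:

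- 402 randomised subjects retain 167 per group for withdrawal of up to 16.9%; or
- withdrawal of 20% leaves about 160 completers per group, compared with the 167 calculated.

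If a power figure is added, word it conditionally: about 89% with 160 per group, if 167 gives 90%. It should not be presented as following from the printed SDs.

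The cost is one reworded sentence, slightly less favourable than the present one, with no extra patients and no change to the design or the analysis. The article describes the trial as not yet recruiting and says that protocol changes will be documented in the registry, so the correction can be recorded there.

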### Randomization

Randomization of this study will be performed as block randomization. Statistical Analysis System Software (SAS) software version 9.4 will be used to generate the blind code of randomization groups with an allocation ratio of 1:1 between the intervention group and the control group. After subjects completing the screen and providing written informed consent forms, the random applicants will apply for a drug number for the subject according to the group to which the subject is randomized via a central randomized system. The drug number of each subject remains the same throughout. If, for some reason, clinical emergencies occur, the personal random code number and random grouping will be made public.

### Blinding

This trial is conducted as a double-blind study. In this double-blind clinical study, researchers, subjects, monitors, statisticians, and data administrators are unaware of the treatment group assignments, which can reduce the bias to the greatest extent. In the event of a clinical emergency, the principal investigator, sponsor, and other people concerned will decide to remove the blindness.

Besides, Mudan granule and placebo granule are indistinguishable in appearance and taste. During the process of placebo preparation, we consider various factors including the properties, production process, prescription and excipients of the original therapeutic drug. Dextrin, pregelatinized starch and microcrystalline cellulose are admixed in varying proportions. As the original therapeutic drug taste bitter, so sucrose octaacetate is added to rectify the taste. The final color results from the addition of food-grade natural caramel pigment. Lastly, Mudan granule and placebo granule are concealed in uniform packages with the same labels.

## Data Collection and Monitoring

### Data Collection

In this study, the Electronic Data Capture (EDC) system will be used for data collection and management. The data collected in the electronic case report form (eCRF) should be consistent with the original medical records, laboratory examination reports and other original documents.

### Design of Electronic Case Report Form

The eCRF should ensure that all data needed for analysis are collected accurately and effectively according to the research protocol.

### Medical Codes

Adverse events will be coded in terms from the Medical Dictionary for Regulatory Activities (MedDRA) (version 22.0) terminology prepared by the International Council for Harmonization (ICH).

### Data Entry and Modification

The data administrators develop the entry instructions/guidelines of the eCRF. All researchers/clinical research coordinators involved in this study will be strictly trained to ensure that the original data is entered into the EDC system accurately, timely, completely and normatively. After data entry, it is not allowed to modify data at will. In cases where there is a need to modify the data, modification reason should be filled in according to the systemic cues. All operations in the system are traceable.

### Blind Review and Database Lock

After the last eCRF entering into the EDC system and all problematic data resolved, the principal researchers, sponsors, statisticians and data administrators will conduct a blind review. Blind review needs to determine which analysis set each case belonging to and how to deal with missing values and outliers.

